##### Processing of the EEG data

The preprocessing of the EEG recordings will be conducted in Cartool Freeware^49^ and will include band-pass filtering (0.1 Hz high-pass and 40 Hz low-pass) and a 50 Hz notch filter, both using a fourth-order non-causal bidirectional Butterworth filter (−24 dB/octave roll-off). Epochs from –100 to 500 ms relative to stimulus onset will be extracted and averaged for each participant and food category to derive the VEPs. Trials will be rejected when voltages at any channel exceed ±100 μV (automated artefact rejection criteria) or visual controls for artefacts (eg, blinks, eye movement). Likewise, channels with poor signal will be excluded. Electrodes will be interpolated using 3-D splines individually for each participant before averaging the data.^50^ Data will then be baseline corrected to the –100 ms prestimulus period and recalculated against the common average reference. After preprocessing, participants with less than 60% of included trials per food category will be excluded from the analyses.

##### VEPs analyses

Differences in brain responses to the stimuli between groups will be assessed using an electrical neuroimaging framework in a multistep analysis procedure that will include both global and local electric field measures.^51
52^

##### Topographic clustering

A topographical clustering analysis will be conducted using hierarchical clustering in Cartool over the 500 ms post-stimulus group-averaged VEPs. This analysis will identify periods of stable scalp electric field topographies (‘template maps’). This analysis is insensitive to differences in response amplitude across the four categories, as data are first normalised by instantaneous GFP. The optimal number of template maps will be determined using the meta-criterion.^53^ A fitting procedure will then assign each time point of each participant’s VEP to the template map that presented the strongest spatial correlation.^54^ This fitting quantifies the preponderance of each template map over a specific time window, which will be analysed using mixed-model repeated measures analysis of variance (rmANOVA). Since topographic differences follow from changes in the underlying source configuration, we will be able to discern whether and when intracranial generator configurations differ between food categories and/or groups.^51^

##### Global field power

To quantify the differences between groups and categories in strength of the VEPs, GFP will be calculated for each participant and food category. GFP is the spatial SD of the electric field of all electrodes and is used to quantify response strength at each time point, considering data from all electrodes simultaneously.^55^ Mean GFP within each time window, based on the abovementioned topographic clustering analysis, will be analysed using rmANOVAs with fat and carbohydrate as within-subject factors and group as the between-subject factors. Significant interactions will be adjusted for multiple comparisons. These analyses will be performed using SPSS.

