### Primary outcomes

The primary outcomes of this study include EEG brain responses to food categories of varying fat and carbohydrate content (HFHC, HFLC, LFHC and LFLC), characterised by the VEP latency, amplitude, duration, topography and neural source activity localisation. Additional primary outcomes include the speed and accuracy of the behavioural responses to food categories of varying fat and carbohydrate content (HFLC; HFHC; LFLC; LFHC) measured by a Go/NoGo smartphone task.

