### Data management and statistical analyses

#### Sample size calculation

The sample size estimation was informed by previous EEG studies of similar design outside of the perinatal context,^23
28
48^ as well as internal pilot data from our group. For EEG outcomes, preliminary data from our previous study (CER-VD 2021-01976) showed a significant fat x group interaction in global field power (GFP) (ηp²=0.103, F(1,37)=4.237, p=0.047; Cohen’s f=0.34). Power analysis assuming an alpha level of 0.05 and 80% power indicated that 35 participants per group were needed. For the Go/NoGo smartphone task used in a different context, pilot data demonstrated group differences in RTs of 550 ms±63 in women with NW and 450 ms±63 in women with OW/OB, at least eight participants per group would be required to detect significant differences in RT assuming an alpha level of 0.05 and 80% power.

Participants diagnosed with GDM at the second visit (approximately 16%) will be excluded in sensitivity analyses. To account for these exclusions and an additional anticipated dropout of 10%–20%, a total of 94 participants (47 per group) with valid data will be recruited. This is expected to result in approximately 37 participants per group at the second visit with valid data, corresponding to the highest requirement derived from our calculations.

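### In the GFP analysis, multiplicity adjustment starts only after an interaction is significant, so seven omnibus F-tests per window go uncorrected, and the one interaction that sizes the EEG sample is not named as the key test.

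*Protocol article*

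**What the plan says.** The Primary outcomes section of the protocol article defines the EEG outcome as responses to four food categories, "characterised by the VEP latency, amplitude, duration, topography and neural source activity localisation". It singles out no feature, contrast or window.

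The Global field power section averages GFP within each window taken from the clustering. It analyses each window by repeated-measures ANOVA, with fat and carbohydrate as within-subject factors and group as the between-subject factor. The rule on multiplicity is one sentence: "Significant interactions will be adjusted for multiple comparisons".

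The number of windows is not fixed in advance. They come from the clustering, for which the Topographic clustering section says: "The optimal number of template maps will be determined using the meta-criterion".

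The Sample size calculation section bases the EEG requirement on a pilot fat × group interaction in GFP (ηp²=0.103, "F(1,37)=4.237, p=0.047", f=0.34) and concludes: "Power analysis assuming an alpha level of 0.05 and 80% power indicated that 35 participants per group were needed". The Go/NoGo reaction time is sized separately: "at least eight participants per group would be required to detect significant differences in RT".

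**The concern.** An adjustment that applies only to interactions already found significant can protect the follow-up contrasts. It cannot protect the step that decides which interactions are significant. Main effects are not mentioned at all, although a difference by fat, carbohydrate or group would answer the first primary objective. The tests are repeated in every window, and nothing corrects across windows.

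At stake is how a positive GFP result can be read. The study is sized for one interaction, but a reader of the results could not tell that hypothesis from the other terms and windows tested beside it, all at 0.05. A chance finding in any of them could be reported as a primary result.

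**Working it through.** **1. The plan's own sample size.** Inputs from the Sample size calculation section: F(1,37)=4.237, f=0.34, alpha 0.05, power 80%.
- ηp² = 4.237/(4.237+37) = 0.103 and p = 0.047, both as printed. f = √(0.103/0.897) = 0.339, printed as 0.34.
- For n per group, use the noncentral F with 1 and 2n−2 df and λ = f²·2n. At n=35, λ = 0.1156 × 70 = 8.09 and power is 80.1%. The stated 35 per group is reproduced, for one test at an uncorrected 0.05.
- Go/NoGo: a difference of 100 ms with SD 63 needs 8 per group by the t-test (power 83.9%), also reproduced.

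**2. Tests per window.** A 2×2×2 mixed design has 3 main effects + 3 two-way interactions + 1 three-way interaction = 7 F-tests. Four of these are interactions.

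**3. Chance of at least one p<0.05 under a complete null.** With w independent windows and k tests per window, the chance is 1 − 0.95^(kw). The values of w are assumptions.

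| Windows (w) | All 7 terms | 4 interactions only |
|---|---|---|
| 1 | 1 − 0.95^7 = 30.2% | 1 − 0.95^4 = 18.5% |
| 2 | 1 − 0.95^14 = 51.2% | 1 − 0.95^8 = 33.7% |
| 3 | 1 − 0.95^21 = 65.9% | 1 − 0.95^12 = 46.0% |
| 4 | 1 − 0.95^28 = 76.2% | 1 − 0.95^16 = 56.0% |

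**4. Correlated windows.** GFP in neighbouring windows is likely to be correlated, so the mixed design was simulated (47 per group, 4,000 runs, all seven terms):

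| Between-window correlation | 3 windows | 4 windows |
|---|---|---|
| 0 | 66% | 76% |
| 0.5 | 62% | 69% |
| 0.7 | 55% | 63% |
| 0.9 | 45% | 50% |

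For the four interactions alone at correlation 0.9, the figures are 29% and 31%.

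**5. Power if the sized interaction is the key test.** With N=94 and f=0.34, λ = 0.1156 × 94 = 10.87. The first Holm step uses alpha = 0.05/w.
- w=1: alpha 0.05, power 90.4%.
- w=3: alpha 0.0167, power 80.3%.
- w=4: alpha 0.0125, power 77.1%.

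For comparison, Bonferroni over all seven terms in every window gives this interaction power of 70.6%, 57.0% and 53.4% at 47 per group for one, three and four windows.

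**The case against.** **The window count is unknown and the null is extreme.** Both are true. Seven tests in one window give about 30%; larger figures need several windows, and the protocol states no number. The Introduction also reports that fat content changes brain responses outside pregnancy, so a fat main effect may be real. Leaving it out reduces the figures only to 1 − 0.95^6 = 26.5% for one window and 1 − 0.95^18 = 60.3% for three independent windows. Interactions alone still give 18.5% and 46.0%.

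**The sentence may mean that all interaction p-values are corrected.** On that generous reading, the three main effects per window remain uncorrected: 1 − 0.95^3 = 14.3% for one window and 1 − 0.95^9 = 37.0% for three independent windows.

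**A fuller analysis plan may set a hierarchy, and some analyses are called exploratory.** A separate plan could do this, and the absence of a hierarchy alone would not be a finding. The point rests on a rule that is printed and does not control the tests it accompanies. The article's remark that several analyses are exploratory does not say which, and these EEG outcomes are listed as primary.

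**Stronger readings the documents do not support.**
- A reader might infer that the whole primary EEG family is uncorrected apart from interactions. The Source estimations section has its own rule of at least 10 contiguous nodes and adjusted post hoc tests.
- A reader might infer that only one test in the study was sized. Go/NoGo reaction time was sized too.
- A reader might double the count for two visits. Longitudinal change is a secondary objective, and nothing says that the primary family is repeated by visit.
- A reader might suspect that windows are picked for GFP differences. The clustering runs on data normalised by GFP, so it does not select on response strength; only the number of windows is left open.

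**Conclusion.** The point holds for the GFP analysis. As printed, the rule leaves the omnibus F-tests uncorrected within and across windows. The resulting error is about 30% for one window and about 60–76% for three or four windows at correlations of 0.5 to 0, falling to about 45–50% at 0.9. Counting interactions alone, it is about 19% for one window and 46–56% for three or four independent windows. These figures assume a complete null and a window count that the protocol does not give. No case examined comes near 5%.

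The EEG sample size is arithmetically sound for one fat × group interaction at an uncorrected 0.05, but the Primary outcomes and Global field power sections do not identify that interaction as the key EEG test. Nothing here shows that the study is too small for the interaction, or that the other primary outcomes are wrongly chosen.

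**What to change.** In the Global field power section:
1. Name the fat × group interaction on mean GFP at visit 1 as the key EEG test, and apply Holm correction to its omnibus p-value across the clustering windows.
2. Replace the present sentence with a rule that the remaining GFP omnibus p-values are corrected, for example by false discovery rate, before any follow-up contrast, and are reported as supportive.

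In the Sample size calculation section, state the resulting power at 94 participants and f=0.34: 90% with one window, about 80% with three and 77% with four at the first Holm step.

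The cost is wording, a routine p-value adjustment, and power slightly below the planned 80% if four windows emerge. Recruitment and data collection are unaffected. Topography, source activity, the Go/NoGo outcomes and the way windows are derived need not change. Naming the sized interaction is what keeps the planned sample adequate: blanket Bonferroni over every term would leave it 57% power with three windows.

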##### Source estimations

Intracranial sources of the VEPs for the four food categories will be estimated using a distributed linear inverse solution based on the Local Autoregressive Average Regularisation Approach (LAURA)^56^ as implemented in Cartool. The head model and lead-field matrix will be computed using the Spherical Model with Anatomical Constraints,^57^ providing current density measures as output, with scalar values at each of 3058 nodes in the solution space. VEPs will be averaged across the predefined time windows (from the topographic clustering) for each participant and food category, and source activity will be computed at each node. RmANOVAs will be conducted using STEN toolbox version 2.0 developed by Jean-François Knebel and Michael Notter (http://doi.org/10.5281/zenodo.1164038) to compare source activity between groups and conditions. Differences in source activity will be considered significant when an activity differed as a function of group and/or condition at the level of individual nodes (p<0.05) and clusters of at least 10 contiguous nodes survive the statistical threshold form a reliable cluster.^48
58^ Post hoc paired and independent sample t-tests with adjustment for multiple comparisons will be performed in SPSS to further investigate within-group and between-group differences.

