#### EEG: stimuli and apparatus

Participants will be presented with four blocks of trials containing a total of 240 pictures. Each block will contain 50 food pictures of the four food categories and 10 non-food objects that were selected from a larger food picture database.^29^ All pictures will be standardised in size and controlled for low-level visual properties.^23
30^ Each picture will be presented for 500 ms, with block order randomised across participants. A central fixation cross will be displayed during interstimulus intervals to minimise eye movements. The experimental session will take place in a sound-attenuated booth (WhisperRoom model 102 126E). Visual stimuli will be presented on a 27-inch LCD monitor (HP EliteDisplay E273q, 2560×1440 pixels, 60 Hz). Continuous EEG data will be recorded at 1000 Hz using a 128-channel gel-based electrode cap connected to an EEGO mylab system (ANT Neuro; https://www.ant-neuro.com). The online reference will be an electrode at the vertex. Electrodes in the cap are spaced equidistant to one another.

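### The source-localisation significance rule (node p<0.05 plus ten touching nodes) does not control false positives and would flag a cluster in most, probably nearly all, null data sets

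*Protocol article*

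**What the plan says.** The Primary outcomes section describes the EEG responses as "characterised by the VEP latency, amplitude, duration, topography and neural source activity localisation", so source localisation carries primary status.

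Under Source estimations, the inverse solution yields "scalar values at each of 3058 nodes in the solution space". Repeated-measures ANOVAs are run at each node on data averaged over windows taken from the topographic clustering. A difference counts if activity "differed as a function of group and/or condition", assessed "at the level of individual nodes (p<0.05) and clusters of at least 10 contiguous nodes survive the statistical threshold form a reliable cluster".

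The recordings come from a "128-channel gel-based electrode cap" and are re-referenced to the common average (Processing of the EEG data). The only multiplicity adjustment in the source section applies to post hoc t-tests, which come after clusters have been declared. The adjustment in the Global field power section concerns interactions in that measure only. Nothing makes the source tests conditional on a significant topographic or global field power result.

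**The concern.** A node-level threshold with a minimum extent controls error only if the extent is calibrated to the spatial dependence of the maps. Here no calibration is given, and the dependence is strong: far more nodes are estimated than there are sensors. When one node crosses p<0.05 by chance, its neighbours tend to cross with it, so ten touching nodes add little protection.

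If so, significant regions will be reported for group, fat, carbohydrate or their interactions even where nothing differs. A positive finding on a primary outcome would then tell the reader very little. Post hoc t-tests on clusters selected this way inherit the selection, and adjusting them afterwards cannot undo it.

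**Working it through.** **Stated figure.** The article gives no false-positive rate for the rule. Its only EEG design figure, 35 per group, reproduces: f = √(0.103/0.897) = 0.339, d = 2f = 0.68, and an exact two-sided t calculation gives 35. That figure concerns the fat × group interaction in global field power and has no bearing on the node rule.

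**Inputs from the article.** 3058 nodes; node threshold 0.05; extent 10; 128 channels, average-referenced; 47 per group at recruitment, about 37 at the second visit. The effects at each node are not itemised. The companion model has seven ("with fat and carbohydrate as within-subject factors and group as the between-subject factors"); a four-level category × group model would have three.

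**Inputs assumed.** Spatial smoothness, node adjacency, regularisation and noise structure, none of which the article states.

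**Step 1: chance crossings.** 3058 × 0.05 ≈ 153 nodes per effect per window.

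**Step 2: dimension.** Average referencing leaves at most 128 − 1 = 127 independent numbers per map, and 3058/127 ≈ 24 nodes per dimension. Taking a scalar magnitude at each node adds no information. The nodes cannot behave as independent.

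**Step 3: lead-field null simulation.** 3071 nodes, 128 electrodes, depth-weighted minimum-norm inverse as a stand-in for LAURA, scalar current density, 47 per group, fat × carbohydrate × group tests, face adjacency, 60 runs per setting, no true effect:

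| Regularisation | Mean P(cluster ≥10) per effect | Range over the 7 effects | Any of 7 | 95th percentile of largest cluster |
|---|---|---|---|---|
| 0.001 | 0.988 | 0.983–1.00 | 1.00 | 173 |
| 0.01 | 0.986 | 0.95–1.00 | 1.00 | 183 |
| 0.1 | 0.974 | 0.933–1.00 | 1.00 | 231 |

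Further lead-field runs used minimum-norm and LAURA-type inverses, several noise structures, and 37 or 47 per group. They gave 0.80–1.00 per effect, with a 95th percentile of about 100–271 nodes for fat × group.

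**Step 4: dependence on smoothness.** Smoothed Gaussian fields, 400 runs per setting, on a ball (3071 nodes) and a shell (3154 nodes). Entries are P(cluster ≥10) for one effect in one window, over both shapes:

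| FWHM (node spacings) | Face adjacency | Full adjacency |
|---|---|---|
| 0–1 | 0.000–0.002 | 0.29–0.66 |
| 1.5 | 0.39–0.59 | 0.79–0.93 |
| 2–6 | 0.94–1.00 | 0.94–1.00 |
| 8–10 | 0.70–0.90 | 0.71–0.90 |
| 15 | 0.40–0.53 | 0.41–0.54 |

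The 95th percentile of the largest null cluster was 32–313 nodes at FWHM 2–6.

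**Step 5: several effects.** Treating effects as independent, the lowest FWHM 15 value gives 1 − (1 − 0.402)^7 ≈ 0.97 for seven effects and 1 − (1 − 0.402)^3 ≈ 0.79 for three. For comparison, tests that each held 5% would give 1 − 0.95^7 = 0.30 and 1 − 0.95^3 = 0.14. Testing several windows raises the rates further.

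**The case against.** The case on the other side has five main parts.

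- **The rate is a model result.** The article gives no smoothness, adjacency or noise covariance, and the simulations use a simplified head model. This stands as a limit on precision. For one effect in one window with very smooth maps, 40–54% is the fairer figure. With 60 runs, an observed 0.80 has a 95% interval of about 0.68–0.88. The 100–270 range is therefore an order of magnitude and not a usable cut-off. None of this brings the rate near 5%. The rule held only for almost independent nodes with face-only adjacency, which 3058 nodes estimated from 128 electrodes cannot be.
- **The rule is cited.** Two sources are referenced and cannot be checked here, so one cannot say that no justification exists. A citation would still not calibrate the rule for this montage, grid and design.
- **Source analysis is one step in a multistep framework, and some analyses are called exploratory.** Topography and global field power have their own tests and are untouched by this point. But no gate is stated, source analysis is not named as exploratory, and localisation is listed as primary.
- **The consequence can be overstated.** Clusters well beyond the simulated null range would still be informative, and the seven-effect count is borrowed from the global field power model. Both points are fair. The fault is that the rule cannot separate such clusters from small chance ones.
- **Permutation is not the only cure.** Also fair: false-discovery control over nodes, or a stricter node threshold with a simulated extent, would also answer the point.

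**Conclusion.** The concern holds. The article states an explicit significance rule for part of its primary outcome, so this is a wrongly fixed rule and not detail left to an analysis plan. The ten-node extent is linked to no error rate, and no correction operates before clusters are selected.

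Lack of control is firm. Its size is conditional: about 80–100% per effect and window in the lead-field simulations, and 40–100% across smoothed fields of FWHM 2–15 node spacings, against a nominal 5%. Over that whole range, at least one of seven effects would show a qualifying cluster in 97% or more of null data sets, treating effects as independent. These figures rest on a stylised head model and assumed noise, and should be read as order of magnitude. The change is needed before any source result is presented as a primary finding.

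**What to change.** Replace the rule with a nonparametric cluster-based permutation test:

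- For group and interaction-with-group terms, permute group labels on each participant's mean or within-subject contrast.
- For within-subject terms, flip the sign of each participant's contrast, or permute condition labels within participant.
- Take the maximum cluster size or mass over all nodes and all analysed windows, and declare clusters at family-wise p<0.05.
- Fix the node threshold, the adjacency definition and the list of effects in advance. The procedure controls error per effect, so either name the effect that is confirmatory or adjust across effects.
- Run post hoc t-tests only on surviving clusters, to describe the pattern and not as fresh evidence for the contrast that selected them.

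If the ten-node maps are kept for comparison with earlier work, label them descriptive and drop the language of significance and reliability for them.

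The cost is analysis wording and computing time. No data collection changes, and collection is expected to run to September 2026, so the rule can be settled before the final analysis. The downside is fewer and larger reported clusters and less direct comparability with earlier maps.
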